## Abstract

The European Alliance against Depression (EAAD) program is to be introduced in The Netherlands from 2017 onwards. This program to combat suicide consists of interventions on four levels: (1) increasing the awareness of suicide by local media campaigns; (2) training local gatekeepers, such as teachers or police officers; (3) targeting high-risk persons in the community; and (4) training and support of professionals in primary care settings. The implementation starts in seven Dutch pilot regions. Each region is designated as a Suicide Prevention Action NETwork (SUPRANET). This paper describes the SUPRANET program components and the evaluation of its feasibility and impact. The findings will be used to facilitate the national implementation of EAAD in The Netherlands and to add new findings to the existing literature on EAAD.

## 1. Introduction

Suicidal behaviour is a global health problem, with over 800,000 people a year dying by suicide [1]. Suicide and suicidal behaviour are the end result of the complex interaction between social, cultural, biological, and environmental factors [2]. The implementation of a multilevel suicide prevention approach potentially increases the success in reducing suicide and is preferred above single, standalone approaches [3,4]. The World Health Organization (WHO) has deemed suicide prevention a global imperative and recommends the development and implementation of a national strategy, in which health and social sectors collaborate. Within national prevention efforts, local communities play a central role in suicide prevention strategies. They can organize social support, prevention, and continuity of care, especially with regard to high-risk individuals, such as middle-aged unemployed men [5].

In 2004, the European Alliance against Depression (EAAD) was founded. The goal was to create a network of experts from different European countries to implement action-focused, community-based public health interventions aimed at depression treatment and suicide prevention [6].

The shared multilevel approach that is currently being disseminated by the EAAD consortium is based on a successful regional intervention in Germany called the Nuremberg Alliance against Depression (NAAD). NAAD was a two year action program combatting depression and suicide in Nuremberg and consisted of interventions on four levels: (1) increasing the awareness of depression by local media campaigns; (2) training local gatekeepers, such as police officers; (3) targeting high-risk people in the community; and (4) training and support of professionals in primary care settings. NAAD resulted in a sustainable decline in suicidal acts (completed and attempted suicides combined) of 24% compared to baseline [6,7,8]. This community-based, four-level intervention has since been implemented in a range of other European countries such as Hungary, Germany, Portugal, and Ireland via the EAAD consortium. Comparable effects to the NAAD were found in Hungary, for example, where a significant decrease in the suicide rate (56%) was observed in the intervention region, which was significantly greater as compared to the control region [9].

As part of the Dutch National Agenda for Suicide Prevention of the Dutch Ministry of Health, 113 Suicide Prevention, the Dutch suicide prevention centre, is introducing the EAAD model in The Netherlands from 2017 onwards. The implementation starts in seven Dutch pilot regions. Each region is designated as a Suicide Prevention Action NETwork (SUPRANET). This paper describes the SUPRANET program components and the evaluation of the feasibility and impact of SUPRANET.

## 2. Program

### 2.1. Selection of Regions

From January 2016 to August 2016, 113 Suicide Prevention has selected seven pilot regions within The Netherlands to implement the Dutch version of EAAD, called the Suicide Prevention Action NETwork (SUPRANET) Community. A SUPRANET Community is defined as a network of local multidisciplinary teams and organizations with shared ownership and responsibility for preventing suicide within a geographical area. The participating communities are committed to embark on a population-focused approach based on the EAAD model to prevent suicidal acts within their population. Members of the network acknowledge that reducing suicidal acts successfully requires concerted action.

Initially, eight regions participated in the selection. One region decided not to continue the selection process because of the lack of commitment and funding. The SUPRANET communities (Figure 1) were selected based on the following criteria:Commitment to suicide prevention expressed by the city council, which is prepared to invest financially;Commitment of local stakeholders in and outside health care to be part of the local network and implement the EAAD components and measure progress;The potential to create a steering group, local project leader and project teams consisting of at least the following key players:
○General practitioner (GP) practices, including GPs and their mental health support staff (POH)○social community teams○mental health care organization○emergency department○citizens/consumer/carer representation○schools and/or employment/social care agencies depending on the high-risk groups targeted by the community.

Furthermore, based on international experiences with the EAAD model, each region had to cover a substantial population, preferably of at least 150,000 inhabitants [10].

### 2.2. Intervention: EAAD Approach

In January 2017 SUPRANET was launched in seven regions in The Netherlands. The intervention of SUPRANET will consist of the implementation of the EAAD model, a two year multi-component multi-setting suicide prevention package with the four components as shown in Figure 2. A summary of each component is outlined below.

#### 2.2.1. Component 1: The Public Awareness Campaign

The public awareness campaigns in the SUPRANET communities will be based on the national campaign launched by 113 Suicide Prevention from February 2017 onwards. This campaign aims to encourage the general public to talk about suicide and to break the taboo. The core message of the Dutch campaign is “Ask the question of your life”. The campaign has three waves in 2017: the first started in February, the second will start in May and the third in September. Based on this national awareness campaign of 113 Suicide Prevention, the SUPRANET communities will start additional, tailored, regional public awareness campaigns in their own communities in May 2017. This includes the release of more posters, flyers, and (radio/online) presentations, specifically tailored to the community. Regions order the materials at 113 Suicide Prevention, which makes the monitoring of the number of ordered materials feasible. The text on the spreading material is specifically tailored to each community. For example the title is altered, containing the name of the region, or the language or dialect is altered to the most common language or dialect in that region.

#### 2.2.2. Component 2: Gatekeeper Training and Reducing Access to Lethal Means

Gatekeeper training programs are recognized as a successful component in multiple intervention projects [11]. Community gatekeepers are trained to identify suicidal risk, to make contact and “open the gates” for help seeking behaviour [12,13]. The gatekeeper training which is most referred to, is based on the method of Question, Persuade, Refer (QPR). Clinical psychologist Paul Quinnett (CEO QPR institute) created the intervention in 1995. In 2012 the gatekeeper training was translated for Dutch usage [14] and since then many community facilitators, such as teachers, student psychologists, police officers, railway employees, and social workers throughout the country have been trained. Within the SUPRANET communities, 113 Suicide Prevention, and some of the mental health organizations, will provide the training sessions.

This program component also covers collaboration with stakeholders, especially those at suicide hotspots (railroads, high buildings) and implementing interventions to reduce access to means, such as providing professionals information about hot-spots for suicide and (the risks of) medication. This important aspect is based on strong evidence for restricting access to means in prevention of suicide [4].

#### 2.2.3. Component 3: Improve Care of High-Risk Groups

Within each community, specific attention will be dedicated to high-risk groups. Examples of high-risk groups are people who received care in the emergency room after a suicide attempt or middle-aged persons (males and females) between 40 and 65 years of age without paid work who receive social assistance or incapacity benefits. In The Netherlands this latter group has a five- to eight-times higher risk of suicide as compared to persons with paid work [5]. This group can be identified by benefit or unemployment agencies. Apart from these groups, regions may prefer to target an additional high-risk group, such as young persons with vulnerabilities due to lesbian/gay/transgender/bisexual (LGBT)- or ethnicity-related issues. During the project, regions will implement interventions that aim to identify and proactively screen members of high-risk groups, and organize access to care for those in need of help. Regions are encouraged to implement evidence-based interventions, which will be exchanged in “best-practice meetups”, organized by 113 Suicide Prevention. However, regions can also opt for expert opinion-based interventions, for instance, successful interventions developed and tested in different, but similar, programs and contexts.

#### 2.2.4. Component 4: Training and Support in General Practice

SUPRANET has a strong focus on change in recognition and treatment of suicidal behaviour in Dutch primary care. Therefore, crucial to each community, is the participation of general practice, notably the general practitioners (GPs) and their mental health support staff (POH). This is a relatively new professional in most Dutch general practices, most often with a nursing or psychological background, providing brief coaching sessions to patients after being diagnosed by the GP. We aim to recruit at least five GP practices within each region. As part of the intervention, a suicide prevention training package is offered to primary care staff in 2017–2018, stimulating the exploration of suicidal ideation and concrete suicide plans among patients. In addition, the practices will work on continuity of care by improving collaboration with social community teams, emergency rooms, and mental health care.

### 2.3. Tailored Intervention

The four-level intervention will be implemented in each SUPRANET community, specified and tailored to local circumstances and to pre-existing suicide prevention structures or interventions. As such, it can be seen as a combination of a top-down and bottom-up approach. This is in line with the EAAD literature, which states that a participatory approach that maximizes and complements what was already in place, is an incentive for participants to become involved in the process [10].

Tailoring includes the option for each region to fine-tune each of the four SUPRANET components and enrich them with local strategies, based on an analysis of the local situation, thus developing a context-specific suicide prevention plan. An example of such fine-tuning is the selection of gatekeepers with whom one might want to work. These could include teachers, youth workers, and sports coaches in an area where the focus is on suicide prevention among youth. When focusing on middle-aged persons without employment, selected gatekeepers could be professionals within employment agencies, social security agencies, debt, counsellors or clergymen. Examples of tailoring the program component in general practice primary care are: the add-on of a depression prevention e-learning module, or the availability of a case manager to ensure continuity of care after hospitalisation.

## 3. Evaluation of the Feasibility and Impact of SUPRANET

The purpose of the evaluation is to investigate the activities of SUPRANET by examining its feasibility and impact on suicidal ideation and behaviour.

This study aims to answer:(1)Does the implementation strategy of SUPRANET lead to the expected EAAD outcomes [6,7,8,9] in terms of:
(a)Reduced suicidal ideation and behaviour and psychological distress?(b)Reduced stigma and taboo and improved attitude towards seeking help?(c)Increased help seeking behaviour to the helpline of 113 Suicide Prevention? (2)Is SUPRANET implemented as intended, in terms of:
(a)What is the reach on each SUPRANET program component (the actors, situations, sites, and contexts involved in the SUPRANET implementation process)?(b)What are the barriers and facilitators when implementing the SUPRANET approach?(c)What is the impact of the interventions on professional performance?

The evaluation of the feasibility and impact on the Dutch SUPRANET communities will be carried out by the research department of 113 Suicide Prevention, NIVEL (Netherlands Institute for Health Services Research), and local Public Health Services in the participating communities.

### 3.1. Design

The multilevel SUPRANET intervention requires a multilevel evaluation approach. Each SUPRANET program component is part of a multi-layered intervention program, therefore, the effect of one component itself is impossible to discern. Since the primary focus of SUPRANET is on preventing suicide, our primary outcomes studying the impact of SUPRANET are on (attitudes toward) suicidal ideation and behaviour. The outcomes and measurements are described in Table 1. Furthermore, the study on feasibility will consist of a process evaluation; studying the reach of SUPRANET on each program component, a qualitative analysis of the barriers and facilitators when implementing the SUPRANET community approach, and the impact of the program on professional performance.

The outcomes are analysed using a non-randomized controlled pre-post design; i.e., the outcomes are analysed compared to a baseline and to national data not involved in the SUPRANET communities. The process evaluation requires qualitative research with stakeholders in all participating regions.

### 3.2. Evaluation of the Impact of SUPRANET

#### 3.2.1. Suicidal Ideation and Behaviour and Psychological Distress of the General Public

Suicidal ideation and behaviour of the general public will be measured in two ways: First, while challenging, because of the low base rate of completed suicide (11 per 100,000 in The Netherlands), suicide rates will be analysed using data from Statistics Netherlands. Trends in suicide rates during 2017–2019 in the seven SUPRANET communities will be compared to the national suicide trends. In 2015, the number of suicides in the SUPRANET communities was 166, on a population of 1,407,331 (11.8 per 100,000). Differences in suicide rates at baseline and after each implementation year will be calculated using incidence rate ratios. The hypothesis is that the multilevel intervention approach of SUPRANET will lead to a reduction in the suicide rate in the general population, as was found in other EAAD studies [6,7,8,9].

Secondly, the scores on the Suicidal Ideation Attribution Scale [15] in an online survey will be analysed. Four measurements will be carried out using on-line questionnaires among the general population. In each measurement, the national sample will be 1000 and the SUPRANET community sample will be 700 (in each SUPRANET community *n* = 100). The sample will be stratified by gender, age, education, region, and social class. The first measurement, the baseline, took place in January 2017. The second will take place just after the first wave of the public awareness campaign, the third in January 2018, and the fourth in January 2019. A fresh sample is taken for each of the four measurements to prevent learning effects and keep the comparison pure over time. Given an alpha of 0.05 and a power of 0.8, the sample will allow us to detect a small effect size of 0.08. The Suicidal Ideation Attribution Scale (SIDAS) consists of five items that are scored from 0 to 10 and assesses the frequency and controllability of suicidal thoughts, as well as the closeness to a suicide attempt, distress and interference with daily activities. We will investigate, using General Linear Model (GLM) repeated measures, if the changes measured in the SUPRANET communities are more improved than the changes measured nationally.

Furthermore, a secondary analysis will be performed on data of the cross-sectional survey Health Monitor 2016. This survey was carried out by all Public Health Services in The Netherlands between September and December 2016 to provide insight into the physical and mental health and lifestyle risks of adults and senior inhabitants. Participants were randomly sampled from municipality registries. Individuals were excluded if they lived in nursing homes, mental health institutions, or if they were imprisoned or were staying in asylums. Based on a sample calculation which took into account the size of the total target population, as well as the expected response rate, approximately 1.1 million inhabitants of 19 years and older were approached. Mental health was assessed by using the validated Dutch version of the 10-item Kessler Psychological Distress Scale (K10). The K10 uses a five-point Likert scale to measure psychological distress, whereby a higher score indicates more distress [16]. The procedure of the Dutch Health monitor 2016 will be repeated in 2020.

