Furthermore, to measure change in guideline adherence, we will look at the key recommendation of the Dutch guidelines, i.e., the exploration of suicidal ideation and concrete suicide plans by GPs and/or primary care nurses [26,27] within the group of depressed patients. We will measure this by making use of a procedure similar to the one used within the sentinel practices of NIVEL Primary Care Database. Monthly, all new contacts for P76 (depressive disorder) within the electronic medical record of the intervention practices will be extracted by a research or doctor’s assistant. The GP or the mental health nurse will be asked to retrospectively answer an additional short questionnaire for each patient about whether or not suicidal thoughts have been explored, what was the level of intensity of the thoughts and concreteness of suicidal plans, and what actions/interventions were proposed/agreed upon. The questionnaire has been developed by experts and based on the recommendations of the Dutch suicide prevention guideline [26], and are added in supplement 1. These are basic elements of the gatekeeper training offered to GPs and mental health nurses in the SUPRANET communities. We will compare the answers of the intervention practices with data collected within a non-randomized group of 40 sentinel practices, a nationally representative subgroup of practices participating in NIVEL Primary Care database with in total 120,000 registered patients (0.7% of the Dutch population). Via these sentinel practices, NIVEL will collect additional data on suicide and suicide attempts over the last 30 years. In these practices an electronic tool incorporated in the EMD of the GP, the P-module, asks for additional information from the GP triggered by the use of an ICPC code, in order to discriminate between cases and non-cases. If a case is defined, the application generates an additional electronic questionnaire about the characteristics of the patient and the content of the GP encounter. In the past 30 years such an additional questionnaire has been used in suicidal patients after fatal and non-fatal suicide attempts indicated by ICPC-code P77 used by the GPs [28]. For the present study a new category has been defined with an extension of the P-module and an extra electronic questionnaire related to TCPC code P76.

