## 4. Discussion

113 Suicide Prevention has the ambition to implement SUPRANET nationwide. The results of this study will help other regions to more effectively tailor the program to their context, important for the national implementation of the EAAD in The Netherlands. The results will be of high relevance for countries in and outside of Europe.

As suicides have been rising since 2007 in The Netherlands, 113 Suicide Prevention believes it is time to really tackle the problem, and directly target suicidal behaviour. While the focus of the public awareness campaign of the EAAD lies on depression, with the secondary aim to reduce suicidal behaviour, in SUPRANET we decided to directly focus on suicide. We believe the specific focus fits well in the Dutch culture, since the Dutch expect others to be open and direct. Furthermore, general practitioners and gatekeepers in The Netherlands are confronted with suicidal behaviour more often than before. Therefore, they understand the need for an intervention with a specific focus on suicide prevention. Regarding the public awareness campaign, we know from the literature that properly communicating about suicide can actually result in less suicidal behaviour (Papageno effect). 113 Suicide Prevention appoints to the subject suicide direct and encourages people to talk about it. Still, as it is a novum to offer a public campaign on suicide prevention in The Netherlands, a safety procedure is built in. As soon as any rise in adverse events are reported, either via the national railways or via other monitors, such as social media, the campaign will immediately be aborted.

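### Suicide rates are to be compared one implementation year at a time with a baseline whose years are not stated; one pooled area-by-period rate ratio would detect much smaller reductions from the same registry

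*Protocol article*

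**What the plan says.** Protocol article, section 3.2.1, gives the method for suicide rates in two sentences. The first sets the comparison: "Trends in suicide rates during 2017–2019 in the seven SUPRANET communities will be compared to the national suicide trends". The second sets the measure: "Differences in suicide rates at baseline and after each implementation year will be calculated using incidence rate ratios". Between them stands the one count supplied: "In 2015, the number of suicides in the SUPRANET communities was 166, on a population of 1,407,331 (11.8 per 100,000". The paragraph does not call 2015 the baseline and does not define the baseline years. It gives no power or detectable effect for this outcome, though it acknowledges that the low base rate makes the analysis difficult.

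Section 3.1 describes a non-randomized controlled pre-post design in which "the outcomes are analysed compared to a baseline and to national data not involved in the SUPRANET communities". Section 4 adds "As suicides have been rising since 2007 in The Netherlands".

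**The concern.** Preventing suicide is the programme's stated primary focus, and suicide is the rarest outcome measured. A separate rate ratio for each implementation year divides few events into smaller parts, and each ratio carries the chance variation of one year. For a count of 166 that variation is about 166 ± 1.96 × √166, or 141 to 191. If the baseline were also one year, that year's luck would enter every yearly ratio.

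A before/after ratio inside the communities also absorbs the rising national trend. The article sets a national comparison beside it but names no single estimate that takes one from the other. A reader of the results could then face three yearly ratios and a separate trend comparison, each imprecise, with nothing fixed in advance as the answer.

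**Working it through.** **Inputs**
- Communities: 166 suicides, population 1,407,331 (section 3.2.1). Check: 166 / 1,407,331 × 100,000 = 11.795, which reproduces the stated 11.8.
- National rate: 11 per 100,000 (section 3.2.1).
- National population: not stated. Section 3.3.4 describes the sentinel practices "with in total 120,000 registered patients (0.7% of the Dutch population", so 120,000 / 0.007 ≈ 17.14 million (16.0 to 18.5 million, given the rounding of 0.7%).
- National suicides: 17.14 million × 11 / 100,000 ≈ 1,886 a year. Rest of the country: 1,886 − 166 ≈ 1,720 a year.
- Assumed: two-sided alpha 0.05, power 0.80, constant yearly counts, Poisson variation only.

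**Formula.** With *a* baseline years, *b* implementation years and true rate ratio *R*, the variance of the log ratio of rate ratios is

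1/(166a) + 1/(166bR) + 1/(1,720a) + 1/(1,720b).

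The detectable *R* solves −ln R = (1.960 + 0.842) × SE. It was solved twice: with the variance at R = 1, which gives the lower figure, and with the variance at the detectable R, which gives the higher one.

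**Worked example, variance at R = 1**
- One against one: SE = √(2/166 + 2/1,720) = 0.115; R = exp(−2.802 × 0.115) ≈ 0.725.
- Five against three: SE = √(1/830 + 1/498 + 1/8,600 + 1/5,160) = 0.0594; R ≈ 0.847.

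**Results, rest of country as control**

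| Baseline years vs implementation years | Detectable reduction | Power for a true 15% reduction |
|---|---|---|
| 1 vs 1 | 27.5–29.6% | 27% |
| 5 vs 1 | 22.1–24.3% | 40% |
| 1 vs 3 pooled | 23.1–23.8% | 40% |
| 3 vs 3 pooled | 17.0–17.7% | 65% |
| 5 vs 3 pooled | 15.3–16.1% | 74% |

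The power column uses the variance at R = 0.85 (for five against three, SE = 0.0623). It therefore belongs with the higher figure in each range. Moving the national population between 16.0 and 18.5 million changes the detectable reductions by about 0.1 percentage point.

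**Where the gain comes from.** Without any control, one against one detects 28.6% (variance at the detectable R); with the rest of the country it is 29.6%. The control costs a little precision and buys protection against the secular trend. The gain in power is due to pooling years.

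**Drift between periods.** Add an assumed SD on the log ratio that does not average out over years. With SD 0.05, the detectable reduction is 31.7% (1 vs 1) and 20.3% (5 vs 3). With SD 0.08, it is 34.5% and 25.1%.

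**Ramp-up.** If 2017 carried no effect and 2018–2019 a 24% reduction, the pooled three-year ratio would be (1 + 0.76 + 0.76)/3 = 0.84. Five baseline years would then give 80% power with all three years pooled, against 96% with 2018–2019 only.

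**Comparator wording.** If the national series did contain the communities, their share of suicides would be 166 / 1,886 = 8.8%. A true ratio of 0.76 would appear as 0.76 / (0.912 + 0.088 × 0.76) = 0.776, so a 24% reduction would show as about 22.4%.

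**The case against.** Four points count on the other side.

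**Comparator.** A reader might infer from "will be compared to the national suicide trends" that the comparator contains the seven communities. The article does not say so. Section 3.1 sets the opposite rule for the outcomes in general, and section 3.2.3 repeats it for crisis calls. The phrase is best read as loose wording, and the effect of inclusion would be small in any case.

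**Baseline.** A reader might also infer a single baseline year, 2015. That year is only described; the launch was in January 2017, and the primary care outcome uses 2016. The baseline may cover several years, and a full analysis plan may say which. This objection stands, but it does not settle the matter: with five baseline years, each yearly ratio still needs a reduction of about 22–24%, because the implementation side is split by year.

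**Secular trend.** It is not ignored, since a national comparison over 2017–2019 is planned. What is lacking is a statement that joins it to the before/after ratio as one estimate.

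**Phased start.** Yearly ratios are reasonable for a programme that builds up: regional campaigns were to begin in May 2017 and primary care training was to run over 2017–2018. Pooling averages in a year of partial delivery, and a long baseline assumes that the community-to-rest ratio was stable. So pooling is not free, and saying that it nearly halves the detectable reduction fits only one against one compared with five against three under pure Poisson variation. Three against three cuts it by about 40%, and starting from one against three the cut to five against three is about a third (23.8% to 16.1%).

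**Conclusion.** The point holds as an inexpensive improvement to a stated analysis choice. The planned yearly rate ratios are individually weak: about 28–30% is detectable against one baseline year and about 22–24% against five. Pooling three years against three brings this to about 17–18%, and five against three to about 15–16%. These figures rest on a constant 166 suicides a year, a derived national count, a two-sided test and Poisson variation only. With an assumed drift SD of 0.08, one against one compared with five against three runs from about 34% to 25%, so the gain is smaller but remains.

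The 24% reduction cited in section 1 for the earlier German programme is a loose benchmark, since it covers completed and attempted suicides together. At that size, one year against one has 61% power and five against three has 99%.

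The documents do not support a claim that the comparator includes the communities or that the baseline is one year. What remains there is a wording mismatch between sections 3.1 and 3.2.1 and baseline years that are not stated.

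**What to change.** - Name the pre-launch years that form the baseline, for example 2012–2016.
- Fit one Poisson or negative-binomial model to annual counts over those years and 2017–2019. Include a population offset and area and year effects, and allow for overdispersion and community-by-period variation.
- Make a single area-by-period rate ratio, the seven communities against the Netherlands without them, the main estimate for suicide rates.
- Keep the yearly rate ratios as descriptive results, so that a build-up over 2017 stays visible.
- In section 3.2.1, word the comparator as in section 3.1.

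The cost is a change of analysis wording and routine annual counts from Statistics Netherlands, the source already named. The downsides are that the pooled ratio averages over the ramp-up year and relies on a community-to-rest ratio that was stable before launch; the pre-launch counts allow the second to be examined.
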